#### **2.1.5 Withdrawal of a Subject**

N/A

### **2.1.6 Subject's Anonymity**

The investigator(s) must ensure that the subject's anonymity will be maintained. On all documents, subjects must be identified only by an identification code and not by their names. A third party (Virtual Surveys) will keep a separate confidential enrolment log that matches identifying codes with the subject's names and addresses.

### **2.2 Protocol Amendment(s)**

Any modification to the agreed protocol must be approved in writing by the sponsor/study co-ordinator and the investigator(s). If alterations have to be made to the protocol after Ethical approval has been given, then the amendments will be submitted for their approval and not implemented until approval is received.

### **2.3 Case Report Form**

N/A

### **2.4 Source Document Verification**

N/A

### **2.5 Adverse Event**

In the current study no treatment or direct intervention is offered and no medical tests are performed. Therefore, it is considered unlikely that subjects will experience adverse event as a result of participation in the study. However, in the unlikely event that such an event occurs, feedback messages in the website have been designed in such a way as to minimise potential excess worry of subjects. Also, subjects presented with the Heart-Age with one highly elevated risk factor or high absolute CVD risk level (30%) can print and take a letter to their GP. This letter will present the GP with information on the study and the Heart-Age tool (Appendix 3). If further information is required the GP will be provided with the name of one of the investigators for discussion.

#### **2.5.1 Adverse Event Definition**

Any untoward medical occurrence in a study subject or administered a treatment and which does not necessarily have to have a causal relationship with the treatment. An adverse event can therefore be any unfavourable and unintended sign (including an abnormal laboratory finding), symptom, or disease temporally associated with the use of a treatment, whether or not considered related to the treatment. Pre-existing conditions that worsen during a study are to be reported as adverse events. They can become Serious Adverse Events if they fulfil one of the seriousness criteria described below.

### **SERIOUS ADVERSE EVENTS**

Any adverse event that fulfils at least one of the following criteria:

- It is Fatal (results in death) (*note*: death is an outcome, not an event).

- It is Life-Threatening (**note:** the term “life-threatening” refers to an event in which the subject was at risk of death at the time of the event; it does not refer to an event which could hypothetically have caused death had it been more severe).
- It requires subject hospitalisation or prolongation of existing hospitalisation (**note:** “inpatient hospitalisation” refers to an unplanned, overnight hospitalisation).
- It results in persistent or significant disability/incapacity.
- It is a congenital abnormality/birth defect.
- It is medically significant or requires intervention to prevent one or other of the outcomes listed above.

Any adverse event that is considered **SERIOUS** must be reported. Since no treatment is offered to subjects and no medical tests conducted there is no such occurrence expected. Please see section 2.5.1

### 2.5.2 Unexpected Adverse Treatment Reaction

An adverse reaction, the nature or severity of which is not consistent with the expected risks of participating in the study.

### 2.5.3 Causality

Causality can be one of three possibilities:

- "NO" (definitely not treatment related)
- "YES" (remotely, possibly, probably or definitely treatment-related)
- "UNKNOWN"

All adverse events judged by either the investigator or the sponsor as being definitely not "NON TREATMENT-RELATED" qualify as Adverse Treatment Reactions.

### 2.5.4 Adverse Event Severity - Definition

The severity/intensity of adverse events can be graded either on a three-point W.H.O. scale (*See W.H.O. Handbook for Reporting Results of Cancer Treatment*) e.g.

- **Mild** or *Grade 1*: discomfort noted, but no disruption to normal daily activities.
- **Moderate** or *Grade 2*: discomfort sufficient to reduce or affect normal daily activities.
- **Severe** or *Grade 3*: Inability to work or perform normal daily activities.

### 2.5.5 Treatment and Follow-up of Adverse Events

All adverse events during the study will be documented and followed up by subject's GP who will be able to involve one of the study's investigators (Appendix 3) until the event is either resolved or adequately explained, even after the subject has completed his/her study.

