## **Risks**

The only potential risk is that some subjects may get unnecessarily worried by their Heart-Age. This is due to the fact that subjects might be presented with higher than expected Heart-Age score.

To minimise this risk a number of actions have been taken:

- a) The Heart-Age tool as a whole is a valid predictor of CVD risk and the model is soon to be published in a high impact cardiology journal. It has also been endorsed by the WHF and the Heart Foundations in each country in which it has been launched.
- b) Feedback messages on the site have been designed in such way as to minimise potential excess worry of subjects. This heart-healthy advice has been seen by the World Heart Federation (WHF).
- c) In all cases, subjects are provided with a message motivating them to visit their GP IF they want to embark on a lifestyle change. Please see Table 1 for a presentation of the different type of messages depending on subjects' absolute risk score. Diabetics will be the only high risk group that will not receive a letter to take to their GP since their health professional would be already aware of their health condition.
- d) The maximum 'Heart Age' that an individual can receive will be capped at 15 years older than their actual age.
- e) Subjects with one elevated risk factor (i.e. being obese; BMI>30) or high absolute CVD level (>30%) can print and take a letter to their GP. This is no different in reality to the current policy in face-to-face clinical studies, where subjects with e.g. high blood pressure are presented by a study nurse with a letter to take to their GP with no further advice.
- f) The Heart Age tool does not suggest that this is a medical advice tool and clearly states that any medical issue should be discussed with a Health Care Practitioner.
- g) The external recruitment agency will be provided with a list of the most frequently asked questions and answers that have been used on the existing Flora-Becel website to be passed on to subjects (if requested). If there are any questions that Virtual Surveys find difficult to handle they will get in touch with the study coordinator.

Table 1. Type of Participant Messages and Absolute Risk Score

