## **10. Serious Adverse Events**

Any adverse event that is considered SERIOUS must be reported within one working day by the investigator to the sponsor/study co-ordinator (for definition see Protocol part III; section 2.5 “Adverse Event”).

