### **3.5 Final report**

A summary will be issued within four weeks of study completion and a final report within 4 weeks of sponsor's comments. This report should include number of subjects enrolled, number of subjects dropped/withdrawn, adverse events, deviations, amendments, statistical analysis and general or specific comments from the investigator. Additionally, the contract laboratory will provide the sponsor/study coordinator with the electronic data.

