#### GP REFERRAL LETTER FOR STUDY SUBJECTS

Re: Patient's Name \_\_\_\_\_  
DOB \_\_\_\_\_/\_\_\_\_\_/\_\_\_\_\_ (DD/MM/YY)

This letter is to inform you that the above-named patient took part in an internet-based health screening study for cardiovascular disease risk using algorithms based on data from the Framingham Heart Study. The study aims to help individuals understand their own level of risk in order to change their current lifestyle.

As part of this study the patient will have been asked for their total cholesterol level, their HDL cholesterol level, systolic blood pressure, whether they were being treated for high blood pressure or diabetic status, in addition to anthropometric measures such as age, gender, weight, height, waist circumference and lifestyle measures e.g. smoking status.

Subsequently individuals are given feedback based on a new "cardiovascular risk adjusted age" i.e. how appropriate their level of CVD risk is for their age – "Heart Age" – (see [www.floraloveyourheart.ie](http://www.floraloveyourheart.ie) for details). They are also given feedback on their individual risk factors, some of which may be unknown to them e.g. cholesterol level

Whilst knowledge of cholesterol and blood pressure is recommended by international guidelines, we do not wish to overburden doctors with requests for more cholesterol testing than is necessary. Therefore we have tailored our advice such that we recommend further testing (e.g. cholesterol test) for those only at potentially high CVD risk (>15% risk in the next ten years). The patient may therefore be asking you whether they need a cholesterol test or blood pressure measurement due to feedback that they may have higher CVD risk or high cholesterol (due to their age, BMI, presence of other risk factors). Of course this is not intended to replace clinical judgement and hope that this has served to facilitate a discussion of CVD risk with your patient

Please contact me on the above number if you would like to discuss this or require further information.

Yours sincerely,

Name            [name]  
Position        Investigator

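### The only designated adverse-event route is the subject's GP, and the letter linking the GP to the study serves Heart-Age subjects only, so capture differs by arm and the one-working-day SAE rule has no defined intake

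*Protocol*

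**What the plan says.** Part III, section 2.5.5 makes the subject's own doctor responsible for recording and following events: "All adverse events during the study will be documented and followed up by subject's GP". The same sentence describes the GP as someone "who will be able to involve one of the study's investigators (Appendix 3"), so the Appendix 3 letter is the named connection to the study team.

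Two sections say who may have that letter. Part III, section 2.5 ties it to the tool: "subjects presented with the Heart-Age with one highly elevated risk factor or high absolute CVD risk level (30%) can print and take a letter". Section 1.5 (Risks), item (e), names no arm: "Subjects with one elevated risk factor (i.e. being obese; BMI>30) or high absolute CVD level (>30%) can print and take a letter to their GP". Item (c) of the same list adds an exception: "Diabetics will be the only high risk group that will not receive a letter to take to their GP".

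Two further sections depend on events reaching the study team. Under section 10 a serious event "must be reported within one working day by the investigator to the sponsor/study co-ordinator". Part III, section 3.5 lists what the final report must hold: "This report should include number of subjects enrolled, number of subjects dropped/withdrawn, adverse events, deviations".

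**The concern.** A GP is not study staff and, on the protocol's text, learns of the study only if the subject prints the letter and brings it. If the letter belongs to one level of a randomised factor, so does the designated path from an event to an investigator.

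Two things are at stake. First, any count of events by arm would reflect who had a letter as well as who had an event. Heart-Age is the component for which section 1.5 acknowledges a risk, so this is the contrast where comparable capture matters most. Second, the investigator has a one-working-day duty for serious events, but nothing says how an investigator comes to hear of one.

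**Working it through.** The protocol gives no adverse-event figure to reproduce. The check sets the passages side by side and then counts the subjects affected.

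**1. Who records events.** Part III, section 2.5.5 names the GP, for all events and without limit by arm. No other section gives the recording to anyone else. The case report form is marked not applicable (Part III, section 2.3).

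**2. What the letter does.** Appendix 3 tells the GP that the patient entered cardiovascular risk data and received a Heart-Age. It is a risk referral that invites discussion. It does not ask the GP to record or report events, so even in the Heart-Age arms the route is incidental.

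**3. Who gets the letter.**
- Part III, section 2.5: subjects shown the Heart-Age with a highly elevated risk factor or high absolute risk. Printing is optional.
- Section 1.5(e): subjects with an elevated risk factor, obesity being the example, or high absolute risk. No arm is named.
- Section 1.5(c): not diabetics.
- Section 5.1, Phase 2: the risk assessment is completed by those going through Heart-Age, and controls receive questionnaires only. The letter would not describe what a Planning or Control subject did.

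Item (e) also stands in a list of measures against worry caused by the Heart-Age. Sections 1.5 and 2.5 therefore differ in wording, but the letter's content fits only the Heart-Age reading.

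**4. Whether anything else asks.** The assessment table in section 5.2 and the Time 1, 2 and 3 questionnaires in Appendix 4 contain no health-event item. The Heart-Age assessment asks about medical history, but only of Heart-Age subjects and before their feedback, so it cannot record later events.

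**5. What needs the information.** Section 10 (serious events within one working day), Part III, section 2.5.3 (causality judged by investigator or sponsor) and Part III, section 3.5 (final report). None says how or when the investigator receives a report.

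**6. Size.** From section 4.1, the arms without Heart-Age hold 100 (Planning) + 100 (Control) = 200 of 400, or 200/400 = 50%. Diabetics in the Heart-Age arms come on top; their number is not stated.

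At Time 2 the number depends on the flow in section 6.2. Reading its two-thirds as retention per step reproduces the planned total: 900 × 2/3 = 600, and 600 × 2/3 = 400. With equal allocation, half of the 600, about 300, would be outside the Heart-Age arms at Time 2. Between Times 2 and 3, 600 − 400 = 200 would be lost, one third of those allocated, so a question asked only at Time 3 would miss them.

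**The case against.** The case on the other side has five parts.

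- **The route is not closed to any arm.** Section 2.5.5 covers every subject, and section 1.5(e) names no arm. The agency escalates difficult questions to the study co-ordinator (section 1.5(g)), the Time 1 instructions give an agency contact, and the Appendix 6 script has a query contact and an open comment box. A Planning or Control subject could use any of these or tell a GP. This stands, and it defeats the inference that those arms will report no events by construction. But these lines are for questions, form difficulties and comments on tasks; none is designated for adverse events.
- **Unseen pages.** The consent form and debrief reach all arms and may carry contact details. This stands as a limit on the finding.
- **The SAE rule still works.** A reader might infer that the one-working-day rule cannot operate. It can, once an investigator knows of an event. What is missing is the defined intake and the start of the clock.
- **The foreseen harm is measured.** Section 1.5 names worry as the only potential risk, and the feedback scale asks at Times 2 and 3 whether the information was worrying. That is fair, but the item rates the information. Part III, section 2.5.1 defines an adverse event as any untoward occurrence, related or not, including worsening of existing conditions.
- **Safety is secondary here.** No treatment or medical test is given, no serious event is expected, safety is not an endpoint, and no event table by arm is planned. The final-report list is general text. This limits the severity. It does not remove the duties in section 10 and Part III, section 3.5, and an expectation of no events cannot be supported by a count obtained without asking.

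**Conclusion.** The point holds in a limited form. The single designated adverse-event route runs through the GP, and its link to an investigator is a letter that, on Part III, section 2.5 and the letter's own text, serves Heart-Age subjects who are not diabetic. Half of the planned completers, 200 of 400, have no designated link. Ascertainment is passive everywhere and differs by randomised arm, so event counts would not be comparable, and the serious-event rule lacks an intake and a clock start.

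The documents do not support a guaranteed zero in Planning and Control, nor the view that no other contact with the study is possible. How much under-reporting would follow cannot be estimated: the protocol gives no event rate and no capture rate. The conclusion assumes that the letter follows section 2.5 rather than the broader wording of section 1.5(e), and that the consent and debrief pages do not already set up a reporting line. It does not touch the primary analysis. It should be corrected because capture that differs by arm is easy to avoid here.

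**What to change.** Reconcile section 1.5, section 10 and Part III, sections 2.5 and 2.5.5, so that one route is described and it is the same in all four arms. Then:

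- **Time 3 item.** Add one identically worded question in every arm on any new or worsening health problem or hospital stay since the Time 2 visit, with space to describe it. Starting at Time 2 keeps the week before allocation out of the counts. Leave out GP visits, because the Heart-Age messages encourage them and the item would then differ by arm.
- **Contact line.** Show the same adverse-event contact to all arms from Time 2, so that subjects who drop out, and those with serious events, can report before Time 3.
- **Routing.** Send entries by study ID to the investigator or study co-ordinator, and start the one-working-day clock on receipt.
- **Reporting.** Present events by allocated arm, and state that capture is self-reported and incomplete for subjects who do not reach Time 3.

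The cost is one online question, one contact line, a forwarding instruction to the agency and a protocol wording change. Someone must read the free text, and ordinary minor illnesses will be reported.

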## 2.6 Publication

Information relating to the study will be kept confidential and publications will be in a form with which the panellist cannot be identified.

## 2.7 Archiving

It is the responsibility of the investigator(s) to maintain adequate clinical study records. Copies of all clinical study material must be archived in the computer electronically (no hard-copies will be kept since this is an online study) for a minimum of five years from completion of the study (or more as legally required). All paper and electronic documents must be archived in a secure place and treated as confidential material.

## 2.8 Audit

The investigator agrees to comply with the sponsor and regulatory authority requirements regarding the auditing of the study.

## 3. Sponsor Responsibilities

### 3.1 General Responsibilities

The project manager/study co-ordinator, the investigator(s) and the study statistician will provide a final draft **protocol**. After mutual agreement, all parties sign the study protocol and submit the protocol to Ethics Committee.

The sponsor/study co-ordinator provides the investigator(s) with **sufficient material** and support to permit the investigator(s) to conduct the study according to the agreed protocol. The sponsor/study co-ordinator reserves the rights to **terminate the study prematurely** for persistent protocol violations, or any other valid and ethical reasons. Should this be the case, the necessary procedures will be arranged after review and consultation by both parties to ensure protection of the subject's interests.

The sponsor provides treatment and/or **compensation** in the case of an injury to, or the death of, a subject, as a result of his/her participation in a study sponsored by them. The sponsor also **insures** the investigator(s) against, or indemnifies them for, losses resulting from liability for such injuries or deaths.

### 3.2 Monitoring and Contract Research Organisation Responsibilities

N/A

### 3.3 Quality Assurance and Quality Control

All material used in studies are subjected to **quality control**. Quality assurance audits may be performed by the sponsor or any health authority during the course of the study or at study completion.

### 3.4 Archives

The protocol, approvals and all other essential documents related to the study must be archived, including certificates that satisfactory audit and inspection procedures have been carried out. All documents must be archived in a secure place for 5 years and treated as confidential material.

### **3.5 Final report**

A summary will be issued within four weeks of study completion and a final report within 4 weeks of sponsor's comments. This report should include number of subjects enrolled, number of subjects dropped/withdrawn, adverse events, deviations, amendments, statistical analysis and general or specific comments from the investigator. Additionally, the contract laboratory will provide the sponsor/study coordinator with the electronic data.

### **3.6 Insurance**

In the unlikely event of any subject suffering any significant deterioration in health or wellbeing arising as a result of taking part in this study, Unilever has undertaken to compensate them without having to prove that anyone involved in this study has been negligent. Any dispute will be referred to an arbitrator.

## APPENDIX 1 - Study Schedule

| Phases                                                                                                       | Processes                                                                                                                                                                                                                                                                                                                                                                                           |
|--------------------------------------------------------------------------------------------------------------|-----------------------------------------------------------------------------------------------------------------------------------------------------------------------------------------------------------------------------------------------------------------------------------------------------------------------------------------------------------------------------------------------------|
| Phase 1:

Recruitment/Screening
(Virtual Surveys)

Pre-Study Assessments | Screening questionnaire (height, weight, health status, age, gender, SES)

Online signing of consent form

Eligible subjects directed to the main Unilever study site to fill out a number of questionnaires                                                                                                                                                                            |
| Duration                                                                                              | 30mins                                                                                                                                                                                                                                                                                                                                                                                              |
| Phase 2

Conduction of main study                                                        | Depending on assigned condition:

-Completion of assessment to enable Heart-Age risk score computation and feedback provided by Heart-Age site

-Questionnaire assessing subject's reactions, perceptions, understanding of the tool and motivation to make lifestyle changes etc

-Subjects being asked to plan how to reduce their saturated fat intake over the next two weeks |
| Duration                                                                                              | Up to 30mins (depending on assigned condition)                                                                                                                                                                                                                                                                                                                                                      |
| Phase 3

Post-Study Assessments

Payment of participants                    | -Follow-up questionnaire assessing subject's reactions, perceptions, self-efficacy, planning behaviour, motivation to make lifestyle changes etc

-Subjects directed back to Virtual Surveys to be reimbursed and have their name entered into a prize draw                                                                                                                                   |
| Duration                                                                                              | 30mins                                                                                                                                                                                                                                                                                                                                                                                              |

